### **9.3. Sample size determination**

The sample size determination was based on a one-sided two-sample *t* test. The sample size estimation is based on the following assumptions:

- One-sided T-test with 2,5 % significance level (equivalent to a two-sided 95 % CI)
- Standard deviation (SD) of the primary endpoint equal to 2
- Non-inferiority margin (NIM) of 1

With these assumptions, we will reach a power of 85 % if we enroll 146 patients. Based on the PallRad study, we assume an exclusion from intention to treat (ITT) - population of around 25 % (8, 9), and we will need to randomize a total number of 200 patients.

This number of patients also provide sufficient power to claim non-inferiority on the exploratory endpoints defined in [Section 9.1](#). The exclusion from ITT set is expected to be lower at 4 weeks, increasing the statistical power of conclusions.

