**Exploratory objectives**

*1. To assess the efficacy of 1-2 fractions of 8 Gy compared to 5 fractions of 5 Gy with respect to:*

- Patient-reported QoL

Endpoint: Change in QoL from BL after 4, 8, 12 and 26 weeks of follow-up

Assessment: European Organization for the Research and Treatment of Cancer Quality of Life Questionnaire-Core15 Palliative (EORTC QLQ-C15 PAL)

- Physician-reported toxicities

Endpoint: All relevant toxicities after 4, 12 and 52 weeks of follow-up

Assessment: CTCAE v 5.0

- Patient reported symptomatic effect

Endpoints: Change in target symptom intensity from baseline after 4, 8 and 26 weeks of follow-up, and changes in intensity of symptoms related to the irradiated tumor other than target symptom (within the five predefined categories) from baseline after 4, 8, 12 and 26 weeks of follow-up

Assessment: NRS score 0-10

- Patient satisfaction

Endpoint: Assessment of patient satisfaction after 4, 8, 12 and 26 weeks of follow-up

Assessment: Patient Global Impression of Change (PGIC)

*2. To explore prognostic models for patient classification*

Endpoint: Correlation between prognostic scores assessed at baseline and overall survival

Assessment: Glasgow Prognostic Score (GPS), LabPS- score and LabBM- score

*3. To explore clinical factors as explanatory response variables*

Endpoint: Correlation between clinical factors and symptomatic response

Assessment: Baseline registration of clinical factors from medical records

*4. Assess hypoxia biomarkers on medical images and biopsies that are previously acquired for diagnosis or treatment, and explore their potential as explanatory response variables in individual patients.*

Endpoint: Correlation between hypoxia biomarkers and symptomatic response

Assessment: Hypoxic fraction assessed by Consumption and Supply-based Hypoxia (CSH)-imaging on MRI (Magnetic Resonance Imaging) and hypoxia-activated protein and gene expression assessed by molecular analyses on tumor biopsies

*5. Assess PD-L1 (Programmed Death-Ligand1)-status in biopsies previously acquired for diagnosis or treatment, and explore potential as explanatory response variable.*

Endpoint: Correlation between PD-L1-status and symptomatic response

Assessment: PD-L1 expression level (all cells) assessed by immunohistochemistry

*6. Compare the health-economic aspects in the two study arms regarding*

- *Patient-reported QoL*

Endpoint: Change in QoL compared to baseline assessed after 4, 8, 12 and 26 weeks

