#### **2.2.2.2. Rectal and Anal Cancer**

A systematic review of palliative pelvic radiotherapy for symptomatic, incurable rectal cancer included mostly retrospective studies using a variety of radiotherapy schedules ranging from 5 to 70 Gy in total radiation doses (3). The studies reported good symptomatic response, but lacked patient-reported and QoL measures. Toxicity results were not evaluable.

In the PallRad study, including patients with rectal cancer, Cameron et al. reported an overall target symptom response of 85% at both the 6-week and the 12-week follow-up visits (8). The QoL remained stable throughout the study period. Patients were treated with a prolonged course of 10-13 fractions, yielding a total dose of 30-39 Gy. The median survival time in the study was 9 months, underlining the limited life expectancy in palliative patients and the importance of reduced overall treatment time.

Another study, including patients with non-resectable or metastatic rectal cancer, evaluated the effect of a short course radiotherapy schedule of 5 Gy in 5 fractions followed by oxaliplatin-based chemotherapy (71). The main outcome was the avoidance of surgery (tumor resection or stoma), and was achieved in 80% of patients. A proportion of 35% of patients had a complete resolution of pelvic symptoms, and 35% had a clinically significant improvement.

In a study on inoperable/elderly patients with rectal cancer, patients were treated with external beam radiotherapy of 39 Gy in 3 Gy fractions in combination with high-dose-rate rectal brachytherapy (72). The study reported good tumor response but a high rate of toxicity.

To our knowledge, there are no studies on palliative radiotherapy of anal cancer.

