### 8.2.1. Patient Reported Outcome Measures

#### 8.2.1.1. Symptom Intensity

Patients will have a target symptom as indication for radiotherapy. Target symptom is the patients main complaint, and will be organized into five predefined categories (pain, bleeding, bowel dysfunction, lower urinary tract dysfunction, vaginal dysfunction). If present, two additional symptoms may be assessed.

Symptom intensity will be reported at baseline as part of clinical routine for decision regarding radiotherapy indication. Patients may require supportive medication adjustments to relieve symptoms pending on radiotherapy. Symptom intensity must be assessed *before* such adjustment, and adjustments shall be performed without any delay.

Symptom intensity will further be assessed after 4, 8, 12 and 26 weeks of follow-up.

Supportive medication corresponding with NRS at all timepoints will be recorded in the eCRF.

Symptom intensity will be measured on a NRS ranging from 0-10, where 0 (no symptom intensity) to 10 (worst symptom intensity imaginable). The following will be measured:

- Average symptom intensity the last 24 hours (primary endpoint)
- Maximum symptom intensity the last 24 hours
- Minimum symptom intensity the last 24 hours

Patients referred from hospitals without radiotherapy might have required adjustments in supportive medications prior to evaluation at the radiotherapy unit. Hence, these adjustments were performed before the patient was considered eligible for study inclusion, but may have reduced target symptom intensity below the limit for inclusion ( $\text{NRS} \geq 4$ ). In these cases, the target symptom intensity prior to adjustments in supportive medications may be registered as baseline NRS as long as registered supportive medications corresponds

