## **9. Statistical Considerations**

### **9.1. Choice of Non-inferiority Margin**

The non-inferiority margin of the difference in the primary endpoint (change in target symptom intensity from baseline after 12 weeks of follow-up) between the two study arms is set to 1 point, which is 50% of the considered minimum clinically important difference based on clinical trials investigating cancer pain (83). The same non-inferiority margin is also currently applied in an ongoing clinical non-inferiority trial (PARASTOP) investigating cancer pain (ClinicalTrials.gov registry number: NCT 05051735). To our judgement, given a different in target symptom relief of less than 1 point, clinicians would prefer radiotherapy with 1-2 fractions of 8 Gy over five fractions of 5 Gy.

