#### **9.5.4. Exploratory endpoints**

Analyses of exploratory endpoints will be regarded as hypothesis-generating post-hoc analyses. Continuous endpoints will typically be analyzed by linear regression or median regression, as appropriate. Dichotomous endpoints will typically be analyzed by logistic regression.

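### Section 9.3 claims non-inferiority power for exploratory endpoints that Section 9.1 does not define and for which the protocol sets no margin or SD

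*Protocol*

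**What the plan says.** Section 9.3 sizes the trial on two assumptions besides the 1-point margin: "One-sided T-test with 2,5 % significance level (equivalent to a two-sided 95 % CI") and "Standard deviation (SD) of the primary endpoint equal to 2". It arrives at 146 patients for 85% power, and at 200 randomized after about 25% exclusion. It then adds: "This number of patients also provide sufficient power to claim non-inferiority on the exploratory endpoints defined in" Section 9.1. The only support that follows is the expectation that fewer patients will be excluded at 4 weeks.

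Section 9.1 concerns one endpoint: "The non-inferiority margin of the difference in the primary endpoint (change in target symptom intensity from baseline after 12 weeks of follow-up"). It names no exploratory endpoint.

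The exploratory endpoints are listed in the synopsis (1.1) and in Section 3. In the synopsis the symptom items begin: "Change in target symptom intensity from baseline after 4, 8 and 26 weeks of follow-up, and changes in intensity of symptoms related to the irradiated". The same lists contain QLQ-C15 PAL, PGIC and EQ-5D-5L. Section 8.2.1.1 says of symptoms beyond the target symptom: "If present, two additional symptoms may be assessed".

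Section 9.5.4 states: "Analyses of exploratory endpoints will be regarded as hypothesis-generating post-hoc analyses".

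**The concern.** A power statement for non-inferiority needs a margin, an SD and a number of evaluable patients. Section 9.3 makes one for a group of endpoints, and the section it points to supplies none of these for any of them. It also gives confirmatory standing to analyses that Section 9.5.4 calls hypothesis-generating.

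What is at stake is how results are presented. On the strength of this sentence, a quality-of-life, 26-week or other-symptom result could be reported as an adequately powered non-inferiority finding, or a failure to exclude the margin could be read as evidence of inferiority. The 4-week result matters more than the rest, because Sections 4.2 and 9.2 attach a practice recommendation to it. Its status is also unsettled: Section 2.1.4 calls it a secondary endpoint at one point, while Sections 1.1 and 3 list it as exploratory.

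**Working it through.** **Inputs from the protocol.** One-sided alpha 0.025, SD 2 (primary endpoint only), margin 1, 1:1 allocation, 200 randomized, about 25% excluded. Median survival in the two earlier cohorts: for rectal cancer, "The median survival time in the study was 9 months" (2.2.2.2); for prostate cancer, 20 months (2.2.2.3). The true difference is not stated and is taken as 0.

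**Formula.** With n patients per arm, total N = 2n, the non-centrality parameter is λ = margin / (SD × √(2/n)). Power is the probability that a non-central t variable with N − 2 degrees of freedom and parameter λ exceeds the 97.5% point of the central t.

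**Step 1: the plan's own figure.** n = 73 gives λ = 1 / (2 × √(2/73)) = 3.02 and power 85.1%; n = 72 gives 84.6%. So 146 reproduces. 146 / 0.75 = 195, rounded up in the plan to 200. Conversely, 200 × 0.75 = 150 evaluable, with power 86.0%.

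**Step 2: does each exploratory endpoint have what the formula needs?**

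| Endpoint | Margin stated | SD stated | Evaluable N stated |
|---|---|---|---|
| QLQ-C15 PAL, PGIC, EQ-5D-5L | no | no | no |
| Other-symptom NRS | no | no | no |
| Target-symptom NRS at 8 and 26 weeks | no | no | no |
| Target-symptom NRS at 4 weeks | no | no | only that exclusion should be lower |

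For the first row, 1 NRS point and SD 2 cannot be carried over, because these are different scales. For the NRS rows the primary endpoint's values can be borrowed, as an assumption.

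**Step 3: target symptom at 4 weeks, SD 2 and margin 1 borrowed.** With no more than 25% excluded, N is at least 150 and power at least 86.0%. At N = 160 it is 88.2%.

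**Step 4: target symptom at 26 weeks, same values borrowed.** The protocol gives no 26-week attrition. Exponential survival at the quoted medians is assumed, with 4.345 weeks per month.

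- 150 evaluable at week 12, then deaths only. The 14 weeks are 14 / 4.345 = 3.22 months.
  - Median 9 months: 150 × exp(−ln 2 × 3.22 / 9) = 150 × 0.780 = 117; power 76.5%.
  - Median 20 months: 150 × exp(−ln 2 × 3.22 / 20) = 150 × 0.894 = 134; power 82.0%.
- Death the only loss among all 200. The 26 weeks are 26 / 4.345 = 5.98 months.
  - Median 9 months: 200 × 0.631 = 126; power 79.6%.
  - Median 20 months: 200 × 0.813 = 163; power 88.7%.

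**Step 5: other symptoms.** Only patients who have the symptom contribute. With SD 2 and margin 1, power drops below 85% once fewer than about 146 patients report it. Of 150 evaluable, that is 146 / 150 = 97%. The protocol does not say what share of patients have a given additional symptom. If 40-70% of 150 did (an assumption), N would be 60-105 and power about 48-72%.

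**The case against.** The strongest reply is that the sentence means only the 4-week target symptom. The next sentence speaks of 4 weeks, and the only non-inferiority conclusion planned apart from the 12-week one is at 4 weeks, in Section 9.2, directly after 9.1. A mis-numbered pointer is plausible, and on that reading the size is adequate at SD 2. This stands as a likely intention, and the fix keeps it. It does not rescue the text: the wording is plural and unrestricted, Section 9.1 never mentions 4 weeks, and the reference is wrong either way.

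It is also fair that Section 9.3 promises sufficient power, not 85%, for these endpoints, and that Section 9.5.4 already tempers how they would be read. A reader might infer that the trial demonstrably misses 85% at 26 weeks and for other symptoms. The documents do not establish that. They give no 26-week attrition, no symptom prevalence and no SD for these endpoints, and Section 9.4 assigns them no analysis set. The most favorable scenario above exceeds 85%, and many would call 82% sufficient.

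A reader might also extend the 25% loss at a constant rate, giving 200 × 0.75^(26/12) = 107 patients and 73% power. That is weaker still. The 25% is an exclusion rate, and under Section 9.4 exclusion from the main analysis set also covers ineligibility, not receiving the allocated radiotherapy, and major deviations, which need not keep accruing after week 12.

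**Conclusion.** Wrong as written; minor severity. From the text alone, the cross-reference leads to no exploratory endpoint, and the power claim has no margin or SD behind it. For QLQ-C15 PAL, PGIC and EQ-5D-5L the claimed property does not exist. For the 26-week target symptom and for other symptoms the claim is unsupported. A shortfall against 85% is probable, but its size depends on borrowing SD 2 and margin 1, on a true difference of 0, and on assumed attrition or prevalence. The 4-week target symptom is not part of the problem, provided SD 2 holds and exclusion is no more than 25%. The sentence conflicts with Section 9.5.4, and the two need reconciling. The primary sample size, margin and analysis are unaffected.

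**What to change.** Delete the sentence in Section 9.3. Alternatively, restrict it to the change in target-symptom NRS at 4 weeks, stating the 1-point margin, SD 2 and the expected evaluable number (power at least about 86% if exclusion is no more than 25%). In either case remove the pointer to exploratory endpoints in Section 9.1. Add that no non-inferiority power is claimed for the remaining exploratory endpoints, which are reported as estimates with 95% confidence intervals in line with Section 9.5.4. If the 4-week statement is kept, Section 9.5.4 should name it as the exception, or the conflict remains.

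Do not write a projected 26-week power into the protocol. The figures above rest on assumptions made for this check and would replace one unsupported number with another.

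The cost is one sentence in 9.3 and, if 4 weeks is kept, a clause in 9.5.4. No patients or data are added. The trial gives up a claim that it could not support.

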## 9.4. Analysis Sets

The following six analysis sets are defined:

- Intention-to-treat (ITT) set
  - All randomized participants with a signed informed consent form
- Full-analysis (FA) set
  - All randomized, eligible participants with a signed informed consent form who has received at least one radiation fraction
- Per-protocol (PP) set
  - All randomized, eligible participants with a signed informed consent form who has received the allocated radiotherapy and completed the follow-up visits at 4 and 12, and 52 weeks without major protocol deviations
- Modified PP set 1
  - All randomized, eligible participants with a signed informed consent form who has received the allocated radiotherapy and completed the follow-up visits at 4 and 12 weeks without major protocol deviations
- Modified PP set 2
  - All randomized, eligible participants with a signed informed consent form who has received the allocated radiotherapy and completed the follow-up visit at 4 weeks without major protocol deviations
- Safety set
  - All randomized participants exposed to radiotherapy

As this is a non-inferiority study, the main analysis of the primary endpoint will be based on the modified PP set 1 of participants having completed all scheduled follow-up visits at the time of assessment (12 weeks).

The main analyses of the secondary endpoints of physician-reported toxicities (CTCAE) at 4, 12, and 52 weeks will be based on the modified PP set 2, modified PP set 1, and PP set, respectively. Safety analyses of physician-reported toxicities will be based in the safety set.

The main analyses of the secondary endpoint of overall survival will be based on the FA set.

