**Number of Participants:**

A maximum of 200 patients will be randomly assigned to study intervention to achieve a per protocol (PP) population of 146 patients

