#### **6.5. Radiotherapy Treatment Course Modification**

The radiotherapy course of patients in arm B can be modified during the intervention if considered necessary by the local clinical oncologist. Modifications include fractionation changes or intervention pauses, and may be initiated as a result of extensive toxicity, deterioration in the general condition of the patient or poor patient compliance. In case of fractionation changes, the total nominal radiation dose received and number of radiotherapy fractions will be recorded in the eCRF. The patient may continue participation in the study if appropriate. If the radiotherapy is paused, a maximum radiotherapy duration of 10 weekdays is allowed, otherwise the intervention must be recorded as incomplete in the eCRF. A patient can resume intervention if considered appropriate by the local clinical oncologist.

If radiotherapy schedule modifications are deemed necessary prior to radiotherapy start in either study arm, the patient must be discontinued from the study.

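### Non-inferiority is decided in modified PP set 1 alone, and the ITT set has no part in the primary decision, so outcome-related loss that differs by arm could produce a false claim

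*Protocol*

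**What the plan says.** Section 9.4 defines six analysis sets. For the primary endpoint, "the main analysis of the primary endpoint will be based on the modified PP set 1 of participants having completed all scheduled follow-up visits". Membership requires four things: eligibility, receipt of the assigned radiotherapy, attendance at both week 4 and week 12, and no major deviation. The only reason given is that the trial tests non-inferiority.

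The decision rule in Section 9.5.2 uses one two-sided 95% interval with a limit of -1. It does not ask for agreement in a second set.

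The ITT set is every randomised patient who signed consent. Sections 9.4 and 9.5 assign it to no analysis. Toxicity uses the PP sets and the safety set. For survival, "The main analyses of the secondary endpoint of overall survival will be based on the FA set", and the FA set leaves out ineligible patients and those who had no fraction.

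Section 6.5 adds a route out of follow-up: "If radiotherapy schedule modifications are deemed necessary prior to radiotherapy start in either study arm, the patient must be discontinued from the study".

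On numbers, Section 9.3 says "we assume an exclusion from intention to treat (ITT) - population of around 25" per cent and randomises 200. The synopsis describes this as being "to achieve a per protocol (PP) population of 146 patients".

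**The concern.** Allocation is open-label and the patients have advanced cancer. Those who worsen, die or stop attending by week 12 leave modified PP set 1. If arm A is truly less effective, a single common tendency for poor responders to drop out removes more patients from arm A. The completers then look more alike than the randomised groups were. Because the rule looks at completers only, nothing in the primary decision would expose this. Section 9.2 ties a standard-of-care recommendation to the result, together with comparable QoL, toxicity and survival.

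The set is also narrower than a week-12 outcome needs. A patient with a usable week-12 NRS is excluded for missing week 4. A patient whose schedule is changed after randomisation but before the first fraction has no outcome at all, although the ITT definition still counts that patient.

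**Working it through.** **Inputs.** Section 9.3 supplies the error rate (one-sided 2.5%), the spread (SD of 2 NRS points) and the margin, listed there as "Non-inferiority margin (NIM) of 1" point. It also supplies about 25% loss and 200 randomised. Allocation is 1:1 (Section 6.3). The true difference is not stated and is taken as 0 for sizing. Differences are A minus B in improvement, so negative values are worse for arm A.

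**The plan's own figure.** By the normal approximation, n per arm = 2 × SD² × (1.960 + 1.036)² / margin² = 8 × 8.98 = 71.8, that is 72 per arm or 144 in total. The t test needs 73 per arm, 146 in total, with power 85.1%. Then 146 / 0.75 = 194.7, so 195, which the plan rounds to 200. The sizing reproduces.

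**How little bias matters.** With 73 completers per arm, SE = 2 × √(2/73) = 0.331 and the 95% half-width is 0.654. Any observed difference better than -1 + 0.654 = -0.346 passes. A bias of 0.1 to 0.2 point is therefore material.

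**Where bias comes from.** Bias = (loss share in A × gap in A) - (loss share in B × gap in B). The gap is the completers' mean improvement minus that of the lost patients.
- Loss 25%/25%, same gap: bias 0, false-claim rate 2.5%.
- Loss 30%/20%, gap of 1 point: bias 0.30 - 0.20 = 0.10. SE = 2 × √(1/70 + 1/80) = 0.327. The rate is 1 - Φ(1.96 - 0.10/0.327) = 4.9%.
- Loss 30%/20%, gap of 2 points: bias 0.20, rate 8.9%.

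**Simulation.** There are 100 patients per arm, SD is 2 and the true difference is exactly -1. One common logistic loss mechanism depends on each patient's own week-12 change, with 25% lost overall. The mechanism is an assumption, not a figure from the protocol.

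| Odds of loss per point less relief | Lost A / B | Completer difference | False-claim rate |
|---|---|---|---|
| 1 (unrelated to outcome) | 25% / 25% | -1.00 | 2.5% |
| 1.28 (log-odds 0.25) | 27% / 23% | -0.95 | 3.4% |
| 1.5 | 28% / 22% | -0.91 | about 4.7% |
| 2 | 30% / 20% | -0.81 | about 9% |

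A steeper slope gives more (15.8% at log-odds 1.0). If loss is outcome-related with the same slope but held at 25% in each arm, the rate stays at 2.5%.

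**If deaths are unrelated to the symptom.** Sections 2.2.2.2 and 2.2.2.3 cite median survivals of 9 and 20 months. Under exponential survival, 12 weeks (2.77 months) leaves 2^(-2.77/9) = 0.81 and 2^(-2.77/20) = 0.91 alive, so death removes 9 to 19%. Making that share of the 25% random lowers the rate to about 3 to 4% at 1.5-fold odds and about 5 to 8% at 2-fold odds.

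**Labels.** The PP set in Section 9.4 requires the 52-week visit. On the same medians, 2^(-12/9) = 0.40 and 2^(-12/20) = 0.66 survive to 12 months, which is 79 to 132 of 200. The synopsis figure of 146 therefore cannot mean that set. It fits modified PP set 1.

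**The case against.** Several points on the other side carry weight.

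- A per-protocol analysis is legitimate in a non-inferiority trial, and ITT alone can also favour non-inferiority when adherence is poor. This stands. The fault is relying on one set, not using the PP set.
- Section 9.4 speaks of a main analysis, and Section 9.5 leaves detail to a SAP that is not at hand. A reader might infer that no ITT analysis will ever be done, but the protocol does not show that. What it does show is that its own decision rule requires none.
- A reader might infer that needing five fractions in arm B and one in arm A also pushes toward a false claim. It probably works the other way. Dropping frail arm B patients who do not complete would make arm B look better and non-inferiority harder to show. Whether arm B patients with altered fractionation belong to the set is not settled either.
- The wording about exclusion from ITT can be read as patients lost on the way from all randomised to those analysed. That reading is natural, and with the synopsis label it leaves the sample size and power intact. Neither is evidence of an underpowered trial.
- The odds ratios for loss are assumed, and part of the loss will come from deaths and deviations unrelated to the symptom. This stands, so the size can only be given as a conditional range.
- A mixed model that assumes missing at random would not remove the simulated bias. With an assumed correlation of 0.5 to 0.7 between early and week-12 scores, the estimated gap moves only from 0.91 to 0.93–0.95, or from 0.81 to 0.85–0.89, against a true 1.0. This also stands and shapes the fix.

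**Conclusion.** The point holds in a bounded form. The trial's sole confirmatory claim rests on modified PP set 1, which is narrower than the week-12 endpoint needs, and the ITT set plays no part in the decision. With a true difference at the margin and 25% overall loss, the false-claim rate is roughly 3 to 9% instead of 2.5% under the assumed mechanisms. That requires loss which is related to relief and unequal between arms. Unequal loss follows from a common mechanism if arm A relieves less. If loss is unrelated to outcome, or equal in both arms with the same mechanism, there is no inflation. The documents do not support saying that a false claim is likely, nor the higher rates that steeper or arm-specific mechanisms would give.

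**What to change.** 1. Keep modified PP set 1, but define it by an available week-12 NRS and drop the week-4 attendance requirement.
2. Declare non-inferiority only if the lower bound is above -1 in both modified PP set 1 and the ITT set. For ITT, use all NRS collected at weeks 4, 8 and 12, adjusted for baseline NRS and target symptom. State how death before week 12 is handled. Add a missing-not-at-random sensitivity analysis, such as a delta-adjusted or tipping-point analysis, because a missing-at-random model alone is not enough.
3. Reconcile Section 6.5 with the ITT definition by continuing to collect outcomes, with consent, from patients whose schedule is changed between randomisation and the first fraction. This concerns follow-up and analysis only, not how they are treated.
4. Analyse overall survival in the ITT set.
5. As wording only, label the 146 as modified PP set 1 and the 25% as loss from randomised patients.

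**Cost.** The NRS scores are already scheduled (Section 1.2), so this means protocol and SAP text and one further analysis, fixed before database lock. Assume a true difference of 0 and, since the protocol gives no figure, 165 to 175 ITT patients contributing data. By the normal approximation, power then goes from 86.5% (150 in modified PP set 1) to 85.3% with 175 in ITT, or from 85.6% (146) to 84.3% with 165. The loss is about 1 to 2 points, depending on how many ITT patients contribute.

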### **2.2.2.4. Gynecological Cancer**

In an observational, retrospective study from 1986, Halle et al. studied the effect of a single fraction of 10 Gy to the pelvis in advanced cancers of the cervix or endometrium (73). The fraction was repeated once or twice at monthly intervals when necessary. The study reported acceptable symptomatic response, but serious side effects were observed in patients surviving more than approximately one year. The authors therefore concluded that 10 Gy fractions should be limited to patients with a life expectancy of less than 12 months.

A similar retrospective Norwegian study, also employing a schedule with one single 10 Gy fraction, was conducted in 2001, and included patients with a life expectancy of less than 12 months (74). However, 28 % of the patients survived beyond 12 months, demonstrating the challenge with lifetime predictions. The study reported a good response on bleeding and vaginal discharge, but serious bowel complications occurred from 9 months onward after radiotherapy.

In a more recent, retrospective study from 2011, another regimen with a single fraction of 8 Gy, repeated at day 7 and 21 if feasible and necessary, was used (75). The study reported effective and rapid symptomatic responses with acceptable toxicity.

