### **9.5.3. Secondary Endpoint**

Data will be reported as means, 95 % confidence intervals, medians or frequencies as appropriate CTCAE:

For all; comparison between the two study arms

1. Number of events any grade, any CTCAE category
2. Number of events grade 1-2 vs grade 3-4, any CTCAE-category
3. Number of events any grade, by CTCAE-category
4. Number of events grade 1-2 vs grade 3-4, by CTCAE category
5. Number of patients with event, any CTCAE category
6. Number of patients with events grade 1-2 vs grade 3-4, any CTCAE category
7. Number of patients with events any grade, any CTCAE category
8. Number of patients with grade 1-2 vs grade 3-4 event, by CTCAE category

CTCAE categories: Gastrointestinal, urinary, reproductive system, constitutional, other

Overall survival:

Kaplan Meier- curves compared with the log-rank test and univariable and multivariable Cox proportional-hazards regression analyses

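### The main toxicity comparison rests on per-protocol completer sets, which toxicity and death can deplete; the severity split has no place for grade 5, and the synopsis attaches 146 to the wrong set

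*Protocol*

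**What the plan says.** Section 9.4 defines three nested per-protocol sets. Each requires eligibility, the allocated radiotherapy and no major deviation. They differ in the visits that must be completed: week 4 (modified PP set 2), weeks 4 and 12 (modified PP set 1), or weeks 4, 12 and 52 (PP set). The main analyses of physician-reported "toxicities (CTCAE) at 4, 12, and 52 weeks will be based on the modified PP set 2, modified PP set 1" and the PP set respectively. The next sentence adds safety analyses of the same toxicities in the safety set, meaning all randomized patients exposed to radiotherapy. Section 9.5.5 limits safety analyses to tabulations.

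Sections 6.5 and 7.1 foresee modification or discontinuation after the start of treatment only for arm B. Section 6.5 says that changes "may be initiated as a result of extensive toxicity, deterioration in the general condition of the patient or poor patient compliance".

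Section 9.5.3 lists eight toxicity summaries. Four are any-grade counts. The other four use a severity split, for example "Number of events grade 1-2 vs grade 3-4, any CTCAE-category".

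On size, the synopsis would randomize at most 200 patients "to achieve a per protocol (PP) population of 146 patients". Section 9.3 says "we assume an exclusion from intention to treat (ITT) - population of around 25" per cent. Section 9.4 analyses the primary endpoint in modified PP set 1.

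**The concern.** Membership of the main toxicity sets can depend on the outcome being measured. If treatment is stopped because of toxicity and the patient then counts as not having received the allocated course, that toxic case leaves the main comparison. The protocol foresees this only in arm B, so the selection can differ by arm and would make the five-fraction course look less toxic than it is.

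The 52-week set keeps only patients who survive and attend. Someone who has a late event and then dies before the visit is not in it.

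The reason given for a per-protocol analysis, that this is a non-inferiority trial, is attached to the primary endpoint. The toxicity question in Section 2.1.2 is whether the arms differ, and Sections 2.1, 4.2 and 9.2 make comparable toxicity a condition for recommending the short course.

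Two wording faults sit beside this. A fatal event has no class in the severity split. The synopsis promises 146 patients in a set whose definition includes the week-52 visit.

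**Working it through.** **1. The stated sample size.** Section 9.3 gives "One-sided T-test with 2,5 % significance level (equivalent to a two-sided 95 % CI"), "Standard deviation (SD) of the primary endpoint equal to 2", and a margin of 1. A true difference of 0 is my assumption; the protocol does not state one.
- Normal approximation: n per arm = 2 × 2² × (1.960 + 1.036)² / 1² = 71.8, so 72 per arm (144).
- Exact t-test: 72 per arm gives 84.6% power and 73 per arm gives 85.1%, so 146 in total.
- Inflation for a 25% loss: 146 / 0.75 = 195. With 200 randomized, 200 × 0.75 = 150 remain, above 146.

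Both 146 and 200 reproduce.

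**2. Which set can hold 146.** Sections 2.2.2.2 and 2.2.2.3 cite median survival of 9 months (rectal) and 20 months (prostate) from the earlier Norwegian study. I assume exponential survival, S(t) = 0.5^(t/median).

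| Time | Median 9 months | Median 20 months |
|---|---|---|
| 12 weeks (2.76 months) | 0.809, or 162 of 200 | 0.909, or 182 of 200 |
| 52 weeks (11.96 months) | 0.398, or 80 of 200 | 0.661, or 132 of 200 |

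A 50:50 mix gives 106 of 200 alive at week 52. Death alone therefore takes 34% to 60% out of the 52-week set. Starting from the 150 expected to be evaluable at week 12, between 74 and 109 would be alive at week 52.

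For 146 of 200 (73%) to be in the PP set with no other loss, the median would have to be 11.96 × ln 0.5 / ln 0.73 = 26.3 months. At week 12, 146 is feasible. It is the number for modified PP set 1.

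**3. Effect of losing toxic arm B cases (assumed rates).** Let the true grade 3 or higher rate be p in both arms, and let a fraction f of arm B cases be excluded. The observed arm B rate is p(1 − f) / (1 − pf).

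| p | f = 25% | f = 50% |
|---|---|---|
| 5% | 3.8% (gap 1.2 points) | 2.6% (gap 2.4) |
| 10% | 7.7% (gap 2.3) | 5.3% (gap 4.7) |
| 15% | 11.7% (gap 3.3) | 8.1% (gap 6.9) |

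The artificial gap is about 1 to 7 points, against arm A. The protocol gives neither p nor f, so this shows direction and scale only.

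**4. Does a cut course leave the set?** Note a to the schedule of activities counts an arm B course finished on days 6-10 as completed, so a short pause need not exclude anyone. Section 6.5 requires a paused course that runs beyond 10 weekdays to be recorded as incomplete. For a changed number of fractions, the protocol records dose and fractions but does not say whether the course still counts as allocated.

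**The case against.** The strongest reply is that the safety set is already there. Section 9.4 plans an analysis of physician-reported toxicity in everyone exposed, so no treated patient vanishes from all toxicity reporting. That stands, and a reader who inferred that toxic patients drop out of the trial's toxicity data altogether would be wrong. But Section 9.5.3 promises between-arm comparisons with confidence intervals where appropriate, while Section 9.5.5 promises tables only, and the comparison named as main stays per-protocol.

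A reader might also infer that the losses fall mostly on arm B. The documents do not support this. The arm B route is specific to cut courses and depends on an undefined term. Death and missed visits, the larger loss by week 52, affect both arms, and no split is given.

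The direction matters too. Losing toxic arm B cases makes arm A look worse, so this route does not favour a false recommendation of the short course. Section 9.2 ties that recommendation to week 12, not week 52.

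The late-toxicity background should not be pressed. The report in Section 2.2.2.4 that "serious bowel complications occurred from 9 months onward after radiotherapy" concerns a single 10 Gy fraction, and the other 10 Gy study there saw serious effects in patients surviving beyond about a year, whom death before week 52 does not remove. The 8 Gy study in the same section found acceptable toxicity. What remains is that a patient with a late event who dies before the week-52 visit is missing from the main analysis.

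Grade 5 is not lost overall: any-grade counts include it, and Section 10.3.2 has deaths not clearly due to progression reported as SAEs.

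**Conclusion.** The point holds as a fault in the choice of main analysis set for a secondary endpoint, with two wording faults beside it. As written, the main toxicity comparison can be selected on its own outcome in arm B, and at week 52 it excludes about 34% to 60% of randomized patients through death alone. That range rests on exponential survival and on medians from two tumour groups; other pelvic cancers in the trial may differ. The arm B effect depends on how a cut course is classified, and its size cannot be known from the protocol.

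The PP set as defined is very unlikely to reach 146. It is not strictly impossible, because the survival curve is assumed.

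A reader might take 25% off the 146 that Section 9.3 says to enroll and infer a loss of power. That is not supported: the same paragraph randomizes 200, which leaves 150. The sample size and the 85% power are correct. Only the labels are wrong, including the phrase about exclusion from ITT, since the ITT set in Section 9.4 keeps every consented randomized patient.

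**What to change.** - **Section 9.4:** make the safety set the main set for bladder and bowel toxicity at weeks 4, 12 and 52, and keep the PP sets as supportive. For grade 3 or higher events, report cumulative occurrence to each time point with all treated patients as denominator. Report grade 1-2 at the visits, among those assessed.
- **Note the data limit.** Under Section 8.5.1, after week 4 (week 8 after a second fraction) only grade 3 or higher events and SAEs judged probably or definitely related are collected. CTCAE grading at visits is scheduled only at baseline and weeks 4, 12 and 52, so a worst grade since the start cannot be built for grade 1-2.
- **Section 9.5.3:** replace the 3-4 class with 3-5, or add a grade 5 row.
- **Sections 1.1 and 9.3:** state that 146 evaluable patients are needed in modified PP set 1 and that about 25% of the 200 randomized are expected to be excluded from that set. This replaces the wording on enrolling 146 and on exclusion from ITT.

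The cost is protocol and SAP wording, best settled before database lock; no new assessments are needed. The downside is that the late-toxicity analysis then mixes visit-based and event-based data, and the expected 52-week PP size has to be stated as smaller than the synopsis implies.
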